#### Maintenance phase—maintaining and safeguarding partnership

*Core session 5 + booster sessions 4–5: Person-centred activity maintenance plan (6–11 weeks postoperatively)*

The focus of this core session is to help the patient to independently continue with the activity progress as well as to detect potential future relapses and discuss strategies on how to tackle such setbacks*.* The intervention content will be repeated, and based on the patients’ personal preferences, thoughts and needs. Behavioural- and outcome goals will be evaluated, and the patient will receive reinforcing feedback on progressions in physical activity, everyday activity goals and self-monitoring. The patient will be asked to formulate beneficial strategies learned during the intervention and be encouraged to continue working with these strategies in the long term. Potential future barriers for engaging in physical activity will be lifted, and the patient will be asked to solve how to tackle these barriers based on techniques learned from the intervention and receive feedback. The shared health plan will be updated for long-term recovery, and long-term physical activity goals will be set to enable the patient to sustain long-term healthy physical activity.

*BCTs include* behavioural experiments (4.4), a review of behaviour goals (1.5), problem solving/coping planning (1.2), behavioural rehearsal/practice (8.1), goal setting (1.1, 1.3), habit formation (8.3), habit reversal (8.4), and generalization of a target behaviour (8.6).

### Usual physical therapy

The control group will follow the usual physical therapy, meaning physical therapy as is provided at each recruiting site when patients undergoing surgery due to spinal stenosis. As this may differ substantially between clinical sites nationally, data on the frequency and content of physical therapy sessions during the study period will be collected as a control variable at the weekly assessments from the control group. During hospitalization participants in both groups will receive the usual care regarding physical therapy conducted on-site. Such care can differ between sites, but commonly involves early postoperative mobilization such as transferring from bed to sitting, chair rising, and walking the same or the day after surgery.

### Procedure

At baseline (approximately 2 weeks preoperatively) and follow-up (11–12 weeks postoperatively), physical activity, physical capacity and PROMs will be assessed. For physical activity, once the patient has agreed to participate in the study, the study coordinator will mail an accelerometer (ActiGraph GT3X + ; ActiGraph, Pensacola, FL, USA) and written user information to the participant for a 7-day assessment. Thereafter, an independent observer will collect demographic/clinical data and conduct physical capacity tests via video. In case of adverse events during video assessments, the independent observer has been instructed to contact medical care immediately if the patient becomes acutely ill or guide the patient to seek medical care if more of a subacute nature. The patient will fill out the PROMs through a secure digital platform (the application BASS, Karolinska Institutet, Stockholm, Sweden). During the intervention, the participants will also fill out weekly repeated measurements in BASS. These weekly measures will include twelve one-item questions addressing physical activity levels, fear of movement, catastrophizing, self-efficacy, and steps per day. Reminders will be sent out automatically via text message if the participant has forgotten to fill in a questionnaire in BASS. At the end of the study, a telephone-based semistructured interview, with all intervention participants, regarding feasibility aspects and participation will be conducted by the study coordinator. Feasibility data will be collected continuously during and at the end of the study period (see Fig. 3).

**Fig. 3 Fig3:**
[figure not shown]
SPIRIT schedule of enrolment, interventions, and assessments

### Baseline variables and outcome measures

Baseline variables such as age, gender, comorbidity, weight/height, smoking status, educational level, sick-leave status, back and leg pain duration, and previous spine surgery will be collected from the patient. Preoperative cognitive function will be assessed with the Cognitive Performance Scale (CPS) [53]. Pre- and postoperative clinical data such as the type of surgery, analgesic use, complications, length of hospital stay, discharge destination, reoperation, and readmission to the hospital will be collected from the medical records.

#### Physical activity level

Objectively measured by a digital triaxial accelerometer (ActiGraph) via the variables, steps per day, time spent in light physical activity, moderate to vigorous physical activity (MVPA), and time spent sedentary [54].Self-reported physical activity with a two-item questionnaire from the National Board of Health and Welfare in Sweden [55].

#### Physical capacity (digitally)

Postural balance with the One Leg Test [56, 57]Physical function with the Timed Up-and-Go test (TUG) [58]Functional leg strength with the 30 s Sit-to-Stand test (30 s STS) [59]

#### Patient-reported outcome measures (digitally)

The person’s own goals regarding function measured with the Patient-Specific Function Scale (PSFS) [60]Health-related quality of life measured with the EQ-5D 3LGeneral self-efficacy with the General Self-Efficacy Scale (GSE) [61]Pain intensity level in the legs and back reported with the numeric rating scale (NRS)Subjective rating of kinesiophobia with the Swedish version of the Tampa Scale of Kinesiophobia (TSK-SV) [62]Catastrophizing thoughts measured with the Pain Catastrophizing Scale (PCS) [63]Disability measured with the Oswestry Disability Index (ODI) [64]Depressed mood assessed by the Hospital Anxiety and Depression Scale (HADS) [65]

#### Treatment fidelity

To assess treatment fidelity and treatment protocol adherence, we will use a triangulation procedure that combines two different approaches based on Toomey et al. [66], and a third additional strategy to assess dosage. Firstly, the Study PT will use a study-specific manual as support for each core session when delivering the intervention and note on a physiotherapist self-report checklist which treatment components have been used in each session. Secondly, to ensure that the main components of the intervention described in the manual are included, audio-recordings will be made of core sessions and a random selection of these recordings will be evaluated by an assessor experienced in person-centredness and cognitive behavioural therapy (CBT). Thirdly, the treatment dose will be assessed by the number of sessions attended and length of each session in minutes reported by the Study PT, to address an additional aspect of fidelity and adherence [67].

#### Process and resource feasibility

Process feasibility [68] will be administered by the following variables: recruitment, intervention use, and acceptability. Recruitment aspects include the percentage of patients eligible after the screening procedure, as well as the reasons for declining participation or dropping out of the study. Patients who withdraw from the study will also be asked if data collected up until the time point of the withdrawal can be used in the study. Intervention use will be calculated as the ratio of the number of completed treatment sessions versus the number of planned sessions. Acceptability with the digital format and intervention will be evaluated using a semistructured interview at the end of the intervention where all intervention participants will be asked about their experience. The Study PT will answer a questionnaire with specific questions about their experience with the intervention. Furthermore, all study participants and assessors will be asked to complete study-specific questionnaires about their thoughts on the digital data collection format (including both PROMs and physical capacity tests) and using the accelerometer. The self-reported physical activity level at screening will be compared with accelerometer data at baseline to evaluate the chosen questionnaire’s ability to detect patients with a low level of physical activity. Treatment safety will be addressed by the type and frequency of possible adverse events during the intervention collected by the Study PT after each session.

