#### Research questions in relation to process and resource feasibility

(5)What percentage of patients planned for decompression surgery for lumbar spinal stenosis meeting inclusion criteria are eligible after the screening procedure?(6)What are the reasons for declining participation in the study or dropping out?(7)Is the screening questionnaire measuring physical activity level able to detect patients with a low level of physical activity compared to accelerometer data at baseline?(8)How many of the planned sessions of the Get Back_feasibility_ intervention do patients of the intervention group attend?(9)Did the study participants and physical therapists (PT) in the study find the digital format, Get Back_feasibility_ intervention, and outcome measures relevant and usable?(10)Is the Get Back_feasibility_ treatment safe (type and frequency of adverse events)?(11)What is the response rate of the used PROMs and to what extent are physical tests completed? If they are not completed, what are the reasons?

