### Intervention content and procedure

Get Back_feasibility_ will be delivered by a physical therapist (Study PT) via video and telephone, enabling patients to access the intervention from their homes. Video communication will be conducted on the Doctrin platform (provided by Doctrin AB), which is an approved medical device, and all data will be processed according to the Swedish Patient Data Act and the EU Data Protection Regulation (GDPR). Get Back_feasibility_ includes five treatment sessions with predefined aims and content delivered through videocall (core sessions) and five shorter reinforcing telephone sessions (booster sessions). Each core session will last for approximately 1 h, and each booster session will last < 30 min. Out-of-session tasks [45] will be formulated at every session and followed up at the next. The intervention will span over 12 weeks (1 week preoperatively until 11 weeks postoperatively). The Study PT will have experience and education in PCC and pain. All parts of the intervention are based on a person-centred approach and are theoretically based on the modified version of the fear-avoidance model [27, 42]. Should unexpected findings of a medical nature be observed during any of the sessions with the study physical therapist, these will be discussed with medical experts in the research group. The sessions and included Behavioural Change Techniques (BCTs) according to the BCT taxonomy [46] are described below and illustrated in Fig. 2.

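### Adverse events for research question 10 are collected only through Get Back sessions, so events outside the medical records have no like-for-like collection in the control arm

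*Protocol article*

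**What the plan says.** Research question 10, in the list on process and resource feasibility, defines safety in brackets: "treatment safe (type and frequency of adverse events". The outcome section Process and resource feasibility then states how it is measured: the "type and frequency of possible adverse events during the intervention collected by the Study PT after each session".

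Intervention content and procedure identifies the Study PT as the therapist who treats: Get Back "will be delivered by a physical therapist (Study PT) via video and telephone". The same section plans five core and five booster sessions. Under Usual physical therapy, the control arm receives whatever its site normally provides, and "data on the frequency and content of physical therapy sessions during the study period will be collected as a control variable at the weekly assessments".

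Procedure describes the weekly digital form as "twelve one-item questions addressing physical activity levels, fear of movement, catastrophizing, self-efficacy, and steps per day". For the video assessments it adds that "the independent observer has been instructed to contact medical care immediately if the patient becomes acutely ill".

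Baseline variables and outcome measures lists a separate source: "complications, length of hospital stay, discharge destination, reoperation, and readmission to the hospital will be collected from the medical records". No arm is singled out there. Statistical methods says that feasibility data are reported descriptively.

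**The concern.** Every patient in this study is recovering from spine surgery, so some falls, pain episodes and unplanned health-care contacts can be expected in both arms. Get Back also sets out to raise walking and to expose patients to activities they avoid. An event count from the Get Back arm alone cannot show how much belongs to the programme and how much to ordinary recovery.

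The route is also tied to the intervention itself. The chance to record an event follows the session calendar and the patient's attendance, and attendance is one of the uncertain outcomes under study (research question 8). The person recording is the person delivering the treatment.

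What is at stake is the usefulness of the answer to question 10 when the full trial is designed, and a missed opportunity to try out two-arm adverse-event collection in a study meant to test trial procedures.

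**Working it through.** The article gives no adverse-event rate, safety threshold or power figure, so there is no stated number to reproduce. The check compares the possible sources and counts the collection points.

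**1. Sources that could capture an adverse event**

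| Source (article section) | Arms | Depends on sessions? | Names adverse events? | Linked to question 10? |
|---|---|---|---|---|
| Study PT after each session (Process and resource feasibility) | Get Back only | Yes | Yes | Yes |
| Medical records (Baseline variables and outcome measures) | No restriction | No | Complications, reoperation, readmission | Not stated |
| Twelve weekly items (Procedure) | Both | No | No, by the themes listed | No |
| Control-arm weekly therapy data (Usual physical therapy) | Control | No | No | No |
| Independent observer at video assessments (Procedure) | No restriction | No | Response instructed, recording not stated | No |
| Reasons for dropping out (question 6) | No restriction | No | No | No |
| End-of-study interview (Procedure) | Get Back only | No | Not a named topic | No |

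Only the first row is both an adverse-event source and tied to question 10, and it exists in one arm.

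**2. Collection points through that route**

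- Get Back: 5 core + 5 booster = 10 at most.
- Core sessions 1 and 2 are preoperative, so 10 − 2 = 8 at most after surgery.
- By the session headings these are 1 at week 1 (core session 3), 4 in weeks 3–6 (core session 4 and boosters 1–3) and 3 in weeks 6–11 (core session 5 and boosters 4–5).
- Control: 0, because control patients have no Study PT sessions.
- If collection happens only at attended sessions (an assumption), the 10 points shrink with attendance: 10 × 0.7 = 7 at 70% and 10 × 0.5 = 5 at 50%.

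**3. What a control-arm rate could and could not offer**

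The event rates below are assumptions. For n = 15 per arm, two-sided 5%, normal approximation:

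power ≈ Φ{ [ |p₂ − p₁|√n − 1.96√(2p̄(1 − p̄)) ] / √(p₁(1 − p₁) + p₂(1 − p₂)) }, with p̄ = (p₁ + p₂)/2.

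- 10% vs 20%: Φ{(0.387 − 0.990)/0.500} ≈ 11%
- 10% vs 30%: Φ{(0.775 − 1.109)/0.548} ≈ 27%
- 10% vs 50%: Φ{(1.549 − 1.270)/0.583} ≈ 68%

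Matching collection would give context for the Get Back count. It would not give a useful comparison test.

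**The case against.** The strongest reply is that safety data do exist for both arms. Medical records supply complications, reoperations and readmissions regardless of arm, attendance or therapist. Leg and back pain and disability are also measured at baseline and follow-up, so lasting worsening would show. This stands. A reader might infer that the control arm has no safety data at all, and the article does not support that. What is left uncovered is the milder or transient event that never reaches the records.

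Second, a reader might infer that patients who stop attending are lost and that the count is therefore biased downwards. That goes beyond the text. Collection after each session does not rule out contact after a missed one, and reasons for dropping out or the coordinator's end interview could reveal some events. None of these is a stated adverse-event source, however, and for withdrawn patients the article describes use only of data collected up to withdrawal, with their agreement. Under-capture is possible but not shown.

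Third, question 10 is descriptive and promises no comparison between arms. This also stands: the plan does not contradict its own aim. A one-arm count is simply hard to interpret after surgery.

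Fourth, the article is condensed. It gives the themes of the weekly items but not their wording, and the schedule figure is not available here. This limits confidence. Still, the article does state the collector, the timing and the setting, and the route it states is one-armed.

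**Conclusion.** The point holds in a limited form. As described, adverse-event ascertainment for question 10 is asymmetric (up to 8 postoperative collection points per Get Back patient, none per control patient) and depends on session contact with the unblinded treating therapist. The consequence is confined to events outside the medical records. Record-based complications, reoperations and readmissions are available without arm restriction, but the article does not say that they feed question 10.

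This rests on two assumptions: that the listed themes of the weekly items are complete, and that no further adverse-event collection is set out in material not shown. Confidence is moderate. The matter is a worthwhile and inexpensive improvement to a descriptive feasibility outcome. It does not invalidate the study.

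**What to change.** Add one identical adverse-event item to the weekly BASS assessment, for example covering a fall, new or worsened symptoms, or an unplanned health-care contact. Ask it of every randomised patient on the same schedule, whether or not Get Back sessions are attended. State that question 10 will be answered by type and frequency, reported descriptively by arm, from this item together with the medical-record data on complications, reoperation and readmission. Keep the Study PT reports as a separate, non-comparative source.

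The cost is one more item on a form that already has twelve and already sends automatic reminders, plus a minor amendment. Respondent burden rises slightly. Enrolment began in April 2023, so patients already followed will lack the item, and that gap should be reported. Weekly self-report also loses patients who stop responding, so the number answering should be given by arm and week. No between-arm significance test should be attached to the result.

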### Sample size

Based on previous literature, the minimum sample size for assessing process and resource feasibility is *n* = 24 [68, 69]. The justifications for this sample size are based on a rationale for the feasibility, precision in the mean and variance, and regulatory considerations. We will include 15 patients in each group (*n* = 30 in total) to leave some margin for withdrawals.

### Statistical methods

Feasibility data will be analysed and reported descriptively. Demographic and clinical data will most likely be reported using a nonparametric approach, such as proportions and medians together with adequate approaches for describing variability, such as interquartile ranges or 95% confidence intervals. Similarly, we will also use nonparametric inferential tests for tentative analyses of efficacy and changes in outcomes within and between groups. In addition, data from the repeated measures will be plotted and analysed visually regarding changes in slope, medians, variability and regarding systematic patterns in these factors within and across participants [70]. The significance level will be set at a *p* value of 0.05. Numeric data will be analysed using the latest versions of IBM SPSS Statistics and/or RStudio. Accelerometer data will be analysed using ActiLife version 6 software. A wear time of a minimum of 10 h per day for at least 4 days will be considered valid [71]. Physical activity data will be reported as average steps per day, as well as minutes per week in each intensity category. We will calculate the proportions of patients who reached < 5000 steps per day (sedentary lifestyle), 5000–7499 steps per day (low active), 7500–9999 (somewhat active), and ≥ 10,000–12,499 steps per day (active) [72]. The proportion of participants in each physical activity level category as well as the proportion reaching the recommendations for health-promoting physical activity made by the WHO will be presented numerically and graphically. Data from the individual telephone interviews with the intervention participants will be transcribed verbatim. The text material will be analysed using inductive content analysis with a descriptive manifest approach.

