## Background

Lumbar spinal stenosis (LSS) is the most common indication for surgical treatment in the lumbar spine [1]. LSS often causes neurogenic claudiocation which in turn limits walking ability. The surgical preference for LSS is decompression [2] aiming at relieving pain, and increasing walking ability and health-related quality of life. Studies suggest that patients with LSS are less likely to meet recommendations for healthy physical activity before and after surgery compared to population norms [3, 4]. Physical inactivity before surgery for LSS is associated with less improvement in postoperative disability and pain [5]. Since people who are physically inactive have an increased risk for noncommunicable diseases such as cardiovascular disease, cancers, and diabetes [6], physical activity should be included in pre- and rehabilitation programmes. It is known that people with the lowest levels of physical activity have the largest health-related benefits of increasing their activity [7].

A recent meta-analysis assessing the effect of prehabilitation prior to lumbar spine surgery (LSS included) concluded that there was very low to low certainty for evidence of no additional effect compared to usual care on postoperative physical functioning, pain, and complications [8]. Nevertheless, studies in the meta-analysis included study populations with both high- and low-risk patients, a variety of interventions and the sample sizes were small. One way to reinforce certainty is to target high-risk subgroups, such as people who are deconditioned with low physical activity, in future studies [8]. In addition, a need has been pointed out for studies investigating the combination of pre- and rehabilitation, as the optimal rehabilitation period is still unclear [9, 10].

Previous pre- and rehabilitation programmes for LSS have primarily focused on reducing disability rather than promoting health [11, 12]. A global call suggested health as an overarching strategic approach for people with low back pain [13]. Physical activity is identified as a significant indicator for health and can be used as a valid outcome. To date, outcomes have primarily been evaluated with patient-reported outcome measurements (PROMs) within the research field [14], and it has been questioned how well they capture postoperative physical activity and related health [15].

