For patients with lumbar spinal stenosis, the cardinal functional problem is walking, and poorer walking capacity is associated with lower daily step counts [16]. Since steps per day is associated with a progressively lower risk of all-cause mortality up to 6000–8000 steps per day in people over 60 years of age [17], walking is recommended directly after surgery. Increased walking time and steps per day directly after surgery are associated with reduced pain and opioid use, as well as improved functioning 6 and 12 months after lumbar spine surgery due to a lumbar degenerative condition including LSS [18, 19]. In the current study, steps per day will be the main focus.

Common reasons, as described by patients, for not engaging in physical activity post-surgery are sedentary habits, persistent pain, and fear of reinjury of the spine [20]. There is conflicting evidence regarding the association between preoperative fear of movement/pain catastrophizing and postoperative pain and disability [21–23], and little is known about how fear of movement interacts with physical health outcomes such as physical activity. In a prior study, we found that preoperative fear of movement was a significant predictor of sedentary behaviour at 6 and 12 months after lumbar fusion surgery. A few studies have indicated that pain-related fear of movement is associated with fewer steps per day in patients with degenerative lumbar disease, including LSS [16, 24].

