Due to the argumentation above, Get Back is designed in the format of a person-centred digital programme that aims to support high-risk patients in being physically active after decompression surgery for spinal stenosis. Prior to performing a full-scale randomized controlled trial, we will conduct a feasibility trial to assure and refine the evaluation design and the intervention itself, as recommended by The Medical Research Council [29]. The current version of the intervention, tested in the feasibility study, will be referred to as Get Back_feasibility_. Here we present the protocol of a study with the objective of evaluating whether Get Back_feasibility_ in combination with decompression surgery can provide a detectable change in variables related to the intervention content and to evaluate the treatment fidelity as well as feasibility in terms of the trial procedure, intervention use, and acceptability in patients identified with a low physical activity level and pain catastrophizing or fear of movement.

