#### Research questions pertaining to outcomes relating to the Get Back_feasibility_ content

Do the assessments preoperatively and at 12-week follow-up of steps per day, physical activity and pain catastrophizing, fear of movement and general self-efficacy provide tentative information as to the efficacy of the Get Back_feasibility_ intervention?Do the weekly assessments of single-item questions aiming to measure steps per day, physical activity and aspects of pain catastrophizing, fear of movement and self-efficacy provide additional information regarding the efficacy of the Get Back_feasibility_ intervention, trajectories of change and interrelations between variables?

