### Participants and study settings

Participants will be recruited from two private spine clinics with referrals from the regions, in Sweden: Capio Spine Center Göteborg and Ryggkirurgiskt centrum (RKC), Sophiahemmet, Stockholm. Inclusion criteria: (i) patients planned for decompression surgery (without concomitant fusion) due to lumbar central spinal stenosis; (ii) patients > 18 years of age. Exclusion criteria: (i) patients with malignancy, severe neurological -or rheumatological disease, idiopathic scoliosis, or isthmic spondylolisthesis; (ii) persons unable to understand written information and communicate in Swedish; and (iii) patients with untreated/unstable heart disease that prohibits physical capacity tests. For patients meeting the inclusion criteria, the following screening criteria should also be fulfilled: (i) low level of physical activity (i.e. persons who do not meet WHO’s physical activity recommendations of a weekly minimum of 150 min of physical activity of moderate intensity), and (ii) higher levels of fear of movement or pain catastrophizing, equivalent with scores ≥ 37 on the Tampa Scale of Kinesiophobia (TSK) [33] and ≥ 30 on the Pain Catastrophizing Scale (PCS) [34].

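### Within-arm tests are grouped with between-arm tests under tentative efficacy, although surgery falls between the two measurements in both arms and could by itself produce a change in the Get Back arm

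*Protocol article*

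**What the plan says.** The analysis sentence in the protocol article (Statistical methods) reads: "we will also use nonparametric inferential tests for tentative analyses of efficacy and changes in outcomes within and between groups". The same section adds: "The significance level will be set at a *p* value of 0.05". It does not say which of the two kinds of test carries the efficacy statement.

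The objective at the end of the Background asks whether Get Back "in combination with decompression surgery can provide a detectable change in variables related to the intervention content". The first research question asks whether the preoperative and 12-week assessments "provide tentative information as to the efficacy of the Get Back_feasibility_ intervention". Neither wording mentions the control group.

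Surgery is common to both arms. The inclusion criterion (Participants and study settings) is "patients planned for decompression surgery (without concomitant fusion) due to lumbar central spinal stenosis", and the control arm (Usual physical therapy) receives "physical therapy as is provided at each recruiting site when patients undergoing surgery due to spinal stenosis". The Procedure section puts baseline about 2 weeks before surgery and follow-up 11–12 weeks after it. The Background describes decompression itself as "aiming at relieving pain, and increasing walking ability and health-related quality of life". It also says: "In the current study, steps per day will be the main focus".

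**The concern.** A pre-post comparison inside one arm measures everything that happened between the two assessments. Here that includes an operation intended to improve walking and relieve pain. The comparison cannot divide the change between operation and programme, and a larger sample would not help, because the confounding is complete within the arm. Only the randomised contrast removes it, since both arms have the surgery.

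The plan puts the two kinds of test side by side under tentative efficacy, and the objective can be met on its wording by change in the Get Back arm alone. A surgery effect could then be described as a tentative signal for the programme. The Abstract says the results will inform whether the programme can be taken to a larger trial, so that description matters even in a feasibility study.

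**Working it through.** **The plan's own figures.** There is no efficacy calculation to reproduce: no effect size, SD or power is given. The sample size is consistent, 15 + 15 = 30, against a literature minimum of 24. The margin is (30 − 24)/30 = 20%, or 12 per arm if all of it is used up. The point does not depend on the sample size.

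**Inputs.**
- From the protocol: 15 per arm, 1:1 allocation, nonparametric tests, level 0.05, surgery between the assessments in both arms.
- Assumed: two-sided tests (sidedness is not stated); normally distributed change scores with SD 1; the same surgery-only mean change d in both arms; no added effect of Get Back. The values of d are illustrative because the protocol gives none.
- Tests: Wilcoxon signed-rank within each arm; Mann-Whitney on change scores between arms; 4,000 simulated trials per row. A repeat with 40,000 trials for d up to 0.8 SD agreed to within about one percentage point.

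**Share of trials with p<0.05 when the programme does nothing.**

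| n per arm | d (SD of change) | Within Get Back arm | Get Back significant, control not | Between arms |
|---|---|---|---|---|
| 15 | 0 | 4.7% | 4.3% | 5.1% |
| 15 | 0.3 | 18.0% | 14.6% | 4.6% |
| 15 | 0.5 | 42.1% | 24.7% | 4.2% |
| 15 | 0.8 | 80.2% | 15.8% | 4.2% |
| 12 | 0.3 | 13.9% | 11.9% | 5.0% |
| 12 | 0.5 | 30.8% | 20.9% | 4.3% |
| 12 | 0.8 | 66.5% | 22.0% | 4.3% |

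The within-arm rate rises with the surgery effect. The between-arm rate stays near the nominal level, because d cancels from the difference.

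**One arm significant, the other not.** The arms are independent. If each is significant with probability p, the pattern of Get Back significant and control not has probability p(1 − p). At d = 0.5 and n = 15 this is 0.421 × 0.579 = 0.244, in line with the simulated 24.7%. It cannot exceed 0.25 when both arms share the same p. Counting discordance in either direction doubles it, to 49.2% in the simulation, but only half of that would flatter the programme.

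**Precision of the randomised contrast.** On a normal approximation, the 95% interval for the difference in mean change has half-width t × √(2/n) × SD. With 15 per arm this is 2.048 × √(2/15) = 0.75 SD; with 12 per arm it is 2.074 × √(2/12) = 0.85 SD.

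**The case against.** The strongest reply is that the plan already contains the right comparison. The trial is randomised against usual physical therapy, between-group tests appear in the same sentence, and the analyses are called tentative. The sentence can also be parsed as two items, efficacy on the one hand and changes within and between groups on the other. All of this stands and limits the weight of the point. It does not settle it: nothing in the article reserves efficacy for the between-group result, and calling an analysis tentative lowers the strength claimed without removing confounding.

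The second reply is that surgery may do little to the variables the programme targets, namely steps, physical activity, catastrophizing, fear of movement and self-efficacy. The Background says that patients often fall short of activity recommendations both before and after surgery. It also says that activity did not improve over time in the group's earlier prehabilitation study. This is fair, and it is why the 0.3 SD row belongs in the table. But that study concerned fusion surgery and did find improved functioning and physical capacity. The Background also links poorer walking capacity to fewer daily steps. The size of a surgery-only change is unknown, and a within-arm test needs it to be nil.

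A reader might infer more: that a within-arm p<0.05 will decide whether to proceed, or that significance in one arm only will be read as a treatment effect. The article says neither. Its Discussion says the results will be used to refine content and procedure before a trial of effect, and feasibility data are to be reported descriptively. Nor is this a finding about multiplicity or power. The efficacy question is limited to a few named constructs, outcome hierarchy is commonly left to an analysis plan, and the study claims no efficacy power.

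**Conclusion.** The point holds in a limited form. As written, the plan lets a within-arm pre-post test count towards tentative efficacy, and the objective's wording does not require a comparison with the control arm. Because both arms have surgery between the assessments, such a test cannot separate programme from operation. For assumed surgery-only changes of 0.3 to 0.8 SD, an inert programme would show a significant within-arm change in about 18% to 80% of trials at 15 per arm, or 14% to 67% at 12 per arm. The between-arm test stays at 4–5%. These rates rest on the assumed d, normal change scores and two-sided tests; the confounding itself rests only on the protocol's design.

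The consequence is modest: this is a feasibility study, its efficacy claims are labelled tentative, and the unconfounded comparison is already planned. The change is still worth making, because it alters a stated analysis and removes a bias at almost no cost.

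**What to change.** 1. In Statistical methods, state that within-arm change will be described only (medians with interquartile ranges or confidence intervals), without tests offered as evidence of efficacy.
2. State that any tentative efficacy statement rests solely on the between-arm difference in change from baseline, with its 95% confidence interval.
3. Present steps per day first, in keeping with its role as main focus in the Background, and the other variables after it as estimates with intervals.
4. Reword the objective and the first research question as change relative to usual physical therapy.

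No new data, patients or procedures are needed, and the change can be made although enrolment has begun. The costs are fewer significant results to report and openly wide intervals, about ±0.75 SD of the change score at 15 per arm.
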